### Sample size calculation

2.4

The level of significance (*α*) is set at 0.05 (two-sided test). Type II error (*β*) is set at 0.2, with a test power of 80%. No clinical trial of thread embedding with the same design could be found through a literature review. Therefore, the sample size was calculated by applying the mean difference of 9.29 and the standard deviation of 17.146 for the Facial Disability Index’s Physical score as the primary efficacy evaluation indicator, based on the results of previously conducted, similar clinical trials on the sequelae of FNP (10).

Considering a dropout rate of 20% (11), 71 participants per group will be needed. A total of 142 participants will be assigned to the study: 71 persons per group, with 102 patients (51 in the TEA group, 51 in the control group) at the one medical center and 40 patients (20 in the TEA group, 20 in the control group) at the other medical center. If an institution’s recruitment ends early, additional participants will be recruited competitively to ensure a smooth enrollment process.

### Randomization

2.5

Participants who voluntarily sign the informed consent form will be assessed for their eligibility to participate in the clinical trial based on the inclusion and exclusion criteria. The final selected participants will be assigned to their respective groups using a random allocation table provided by two clinical trial institutes. According to the random allocation details, identification codes will be assigned to participants in the order they were recruited, and treatment will be implemented in each group accordingly. An independent researcher, not affiliated with the main clinical trial team, will employ Excel 2019 (Microsoft Corporation, Redmond, WA, USA) to conduct block randomization. This method will feature a block random assignment and the concealment of block sizes to prevent those responsible for participant recruitment and group allocation from knowing the block sizes (12).

### Allocation concealment

2.6

The random allocation table will be managed by a third researcher not involved in the intervention and evaluation, and the trial personnel, based on the random allocation table, will randomly assign participants by opening the sequentially numbered, opaque envelopes provided by an independent envelope administrator, not related to the study. The random assignment will be predetermined and cannot be changed once carried out. As it is not feasible to blind the interventionists and participants in this study design, evaluator blinding will be implemented. The evaluator who will not participate in the intervention will be blinded to group allocation.

### Intervention

2.7

In the TEA and control group, six electroacupuncture sessions will be performed once a week for 6 weeks. In the TEA group, after completing the acupuncture treatment, the embedding acupuncture treatment will be carried out once a week for 6 weeks for six sessions. During the trial period (6 weeks), no other interventions will be performed apart from the designated treatments. Electroacupuncture and TEA therapies will be performed by a specialist in acupuncture or a specialist trainee under the supervision of a specialist. The interventionists will complete an educational program through a trial supervisor-led workshop to ensure that treatments are conducted according to the established methods in all studies.

#### TEA

2.7.1

TEA will be administered using a 29 G, 25-mm and 38-mm TEA needle (Hyundae Meditech, Wonju, South Korea) on 20 predefined acupoints selected by an expert group of Korean medical doctors according to STRICTA (Table 2 and Figure 2).

**Table 2 tab2:** Details of the TEA using the STRICTA 2010 checklist.

Item	Details	
1. Acupuncture rationale	1a. Style of acupuncture	TEA
	1b. Reasoning for treatment provided	By the consensus of a group of clinical experts, modified from that used in a previous study.
	1c. Extent to which treatment was varied	No variation
2. Details of needling	2a. Number of needle insertions per subject per session	20 acupoints
	2b and 2c. Names of points used and depth of insertion, based on a specified unit of measurement or on a particular tissue level	with 29G × 25 mm (affected side): BL2 to EX-HN 4, EX-HN 4 to TE23, ST1 to EX-HN 7, ST3 to LI19, LI19 to ST4, ST4 to ST6, ST6 to ST7, CV24 to ST4, mental tuberosity to CV24. with 29G × 38 mm (affected side): ST4 to LI20, LI20 to BL1, ST7 to ST4, ST4 to ST6, SI18 to LI20, SI18 to LI19, SI18 to ST4. with 29G × 38 mm (unaffected side): ST4 to ST6, ST7 to ST4.
	2d. Response sought	Thread embedding can produce sensations similar to acupuncture, such as soreness, distension, or heaviness, but the reactions tend to be more pronounced due to the thicker and longer threads used in the procedure.
	2e. Needle stimulation	Thread embedding
	2f. Needle retention time	No retention time
	2g. Needle type	TEA (29G × 25 mm and 38 mm)
3. Treatment regimen	3a. Number of treatment sessions	6 sessions
	3b. Frequency and duration of treatment sessions	Once a week for 6 weeks
4. Other components of treatment	4a. Details of other interventions administered to the acupuncture group	Electroacupuncture
	4b. Setting and context of treatment, including instructions to practitioners, and information and explanations to patients	Minimized conversation between practitioner and patient.
5. Practitioner background	5a. Description of participating acupuncturists	Specialists of the acupuncture and moxibustion department with at least 3 years of clinical experience.
6. Control and comparator intervention	6a. Rationale for the control or comparator in the context of the research question, with sources that justify this choice	Electroacupuncture will be used as a comparator, in this manner, the specific therapeutic effect of TEA will only be displayed.
	6b. Precise description of the control or comparator	0.20 × 30 mm sized acupuncture will be used within 5–20 mm depth. After the administration of acupuncture, electro-stimulation will be applied for 20 min.

TEA, thread embedding acupuncture; STRICTA, standards for reporting interventions in clinical trials of acupuncture.

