**Methods:**

A multicenter, randomized, assessor-blinded clinical trial will be conducted. One hundred forty-two participants will be recruited by eligibility criteria and be randomly divided into two groups. The intervention group will receive thread-embedding acupuncture in addition to electroacupuncture, while the control group will be given only electroacupuncture. The primary outcome is a change in the physical function score of the Facial Disability Index. The secondary outcome is change in Sunnybrook Facial Grading System, Social/Wellbeing function score of Facial Disability Index, Synkinesis Assessment Questionnaire, Numeric Rating Scale of stiffness by facial region, Patient Global Impression of Change, Euro-Qol 5-Dimension 5-level, Economic evaluation questionnaire and adverse events. Assessment points include before treatment (Week 1), after treatment completion (Week 6), 2 weeks post-treatment completion (Week 8, Primary endpoint), and 10 weeks post-treatment completion (Week 16).

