#### Facial Disability Index

2.8.1

The primary outcome measurement is the physical function score with Facial Disability Index. The Facial Disability Index is the patient-reported evaluation questionnaire that consists of a total of 10 items, which are further divided into five items related to physical function (Physical score) and five items related to social/well-being function (Social-Wellbeing score). Based on the scores of individual items, the physical function (Physical score) is calculated out of 100 points, and the social/well-being function (Social-Wellbeing score) is also calculated out of 100 points. With a total of 200 points being the maximum score, a lower score indicates a more severe functional impairment due to facial disorders (14).

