#### Sunnybrook facial grading system

2.8.2

The evaluator assesses facial movement due to FNP and derives a final score within the maximum range of 100 points based on scores for 3 Resting symmetry items, scores for 5 Symmetry of Voluntary Movement items, and scores for 5 Synkinesis items (15).

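### Table 2 item 6a claims that the comparison isolates the specific effect of TEA; with open allocation and a self-reported primary outcome it estimates the effect of adding TEA to electroacupuncture

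*Protocol article*

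**What the plan says.** The Abstract sets out the arms: "The intervention group will receive thread-embedding acupuncture in addition to electroacupuncture, while the control group will be given only electroacupuncture". Section 2.7 confirms that both groups have six weekly electroacupuncture sessions and that the TEA group has thread embedding after each one. No sham thread procedure is described for the control group.

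Table 2 item 6a (section 2.7.1) justifies the comparator: "Electroacupuncture will be used as a comparator, in this manner, the specific therapeutic effect of TEA will only be displayed".

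On blinding, section 2.6 states: "As it is not feasible to blind the interventionists and participants in this study design, evaluator blinding will be implemented".

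On the primary outcome, section 2.8.1 states: "The primary outcome measurement is the physical function score with Facial Disability Index". The next sentence identifies the rater: "The Facial Disability Index is the patient-reported evaluation questionnaire that consists of a total of 10 items". The outcome that the evaluator rates is the Sunnybrook score, a secondary outcome (section 2.8.2): "The evaluator assesses facial movement due to FNP and derives a final score".

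The Introduction describes the aim in other terms. It compares outcomes with and without TEA in a setting close to practice, and it notes that the group's 2020 trial used a sham TEA control.

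**The concern.** Item 6a makes an explanatory claim: what remains after subtracting the control arm is the specific effect of TEA and nothing else. For that to hold, the arms would have to be alike in everything but the specific action of the threads, including what participants believe and experience. Here they differ in both, and the person who scores the primary outcome is the person who knows the allocation. The assessor-blinded label in the title does not reach that score.

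What is at stake is the interpretation of a positive result. Read through item 6a, a significant FDI difference would be credited to the threads themselves. The design supports the narrower statement that offering TEA on top of electroacupuncture improved self-reported function, for whatever mixture of reasons.

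**Working it through.** **Step 1. What cancels and what does not.** Write the expected group difference on the FDI physical score as

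difference = (EA + S + N) − EA = S + N,

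where S is the specific effect of TEA and N collects the non-specific components that occur only in the TEA arm. EA cancels because both arms receive it. Item 6a requires N = 0. Against the protocol:

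| Component | TEA + EA arm | EA arm | Cancels? |
|---|---|---|---|
| Electroacupuncture | six weekly sessions | six weekly sessions | yes |
| Additional procedure | 20 insertions per session, six sessions; item 2d expects stronger sensations than with acupuncture | none | no |
| Knowledge of allocation | knows TEA was given | knows it was not | no |
| Rater of primary outcome | the unblinded participant | the unblinded participant | evaluator blinding does not apply |

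Nothing in the design sets N to zero, and S and N cannot be separated from the FDI difference.

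**Step 2. The plan's own figure.** Inputs from section 2.4: difference 9.29, SD 17.146, two-sided alpha 0.05, power 80%, dropout 20%. The standardised difference is 9.29 / 17.146 = 0.542. A two-sample t-test needs 54.4, so 55 per group. Allowing for dropout, 55 / 0.8 = 68.75, so 69 per group, against 71 stated. That is close, and the sample size is not in dispute here.

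**Step 3. How much a non-specific shift could matter.** The documents give no value for N, so the values below are assumptions and the result is an illustration.

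- Evaluable per group: 71 × 0.8 = 56.8, taken as 57.
- Standard error: 17.146 × √(2/57) = 3.21 points.
- Set S = 0 and let N be 2, 3 or 5 points, all below the planned difference of 9.29.
- N / SE = 2/3.21 = 0.62, 3/3.21 = 0.93 and 5/3.21 = 1.56.

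The two-sided 5% t-test (noncentral t, 112 degrees of freedom) then rejects as follows:

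| Assumed N (FDI points) | 57 per group | 71 per group (no dropout) |
|---|---|---|
| 0 | 5.0% | 5.0% |
| 2 | 9.5% | 10.6% |
| 3 | 15.3% | 17.9% |
| 5 | 33.9% | 40.7% |

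These rates count both directions. At 57 per group and N = 2, about 9.0% favour TEA and 0.5% favour control; at 5 points almost all favour TEA. More participants raise the rate, because N is a bias with respect to S and does not shrink with sample size.

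**The case against.** The strongest reply is that item 6a is one awkward cell in a reporting checklist, and that *specific* there may mean only that the difference is due to TEA and not to electroacupuncture. The rest of the article is pragmatic: the Introduction asks about care with and without TEA, and the Conclusion in the Abstract and the Discussion speak of TEA alongside or combined with electroacupuncture. The lack of participant blinding is stated openly, item 4b limits conversation during treatment, and no passage says that evaluator blinding covers the FDI.

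Much of this stands. The add-on design is legitimate for the pragmatic question, for which the non-specific components are arguably part of the effect; the rejection rates above are then false positives only for a claim of specificity. Limited conversation may reduce contact effects, and since no contact times are given, their size is unknown. What does not stand is the benign reading of the sentence. It says that only the specific effect is displayed, and removing the electroacupuncture effect does not achieve that. Limited conversation also leaves untouched the expectation of a participant who knows which treatment was given.

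Three stronger readings are tempting and are not supported:

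- A reader might infer that the trial needs a sham arm. The Introduction's aim does not require one.
- A reader might infer that the authors will report a specific effect. Neither the Abstract's Conclusion nor the Discussion's statements of aim repeat the claim in item 6a.
- A reader might infer that the baseline FDI is completed after allocation is known. Table 1 puts randomization and the baseline FDI at the same visit without giving their order, and a condensed article may leave that detail to the full protocol.

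**Conclusion.** The claim in item 6a is wrong as written. On the primary outcome, the trial estimates the effect of adding TEA to electroacupuncture, with expectation and the extra procedure included. This conclusion rests only on the stated arms, the stated lack of participant blinding and the stated patient-reported outcome; it needs no assumption about size.

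The size is uncertain. The rates of about 9.5%, 15% and 34% depend on assumed shifts of 2, 3 and 5 points, no specific effect, the planning SD and 57 evaluable per group. They show that shifts well below the planned difference could matter for a claim of specificity, not that such shifts will occur.

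A reader might also infer that comparing the FDI with the blinded Sunnybrook score would reveal whether expectation is at work. It would not. One measures self-reported function and the other rated movement and synkinesis, so a real effect could appear on only one of them. Agreement would not exclude expectation from the FDI either.

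This should be fixed because it changes what the trial may conclude. It does not affect the choice of comparator, the primary outcome, the primary test or the sample size.

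**What to change.** 1. Reword Table 2 item 6a so that the comparator is said to show *the effect of adding TEA to electroacupuncture, including non-specific effects*.
2. Limit conclusions drawn from the FDI to that effect.
3. State expectation and performance bias as a limitation, and say that evaluator blinding does not extend to patient-reported outcomes.
4. Present the blinded-evaluator Sunnybrook result at Week 8 beside the primary result as supportive evidence. Do not treat agreement or disagreement between the two as a test for expectation.

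The cost is a more modest claim and a few sentences of text. Sunnybrook is already scheduled at Week 8 in Table 1, so no new measurement is needed.

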**Figure 2 fig2:**
[figure not shown]
Insertion location of thread embedding acupuncture.

#### Electroacupuncture

2.7.2

Sixteen needles of 0.20 × 30 mm size will be used for administration at the following acupoints at a depth of 5–20 mm. The acupoint locations were determined according to the standard acupoints guidelines provided by the Korean Medicine Convergence Research Information Center (13).

Twelve affected side acupoints are BL2, TE23, GB14, ST3, TE17, ST4, ST6, GV26, CV24, ST7, ST 18 and ST3. Two bilateral acupoints are LI4 and LR3. After the insertion, electrical stimulation will be applied for 20 min at a frequency of 4 Hz, inducing muscle contraction with an intensity that does not cause discomfort to the participants. Stimulated acupoints are BL2 to TE23, ST4 to ST6, SI18 to ST3.

### Outcome measurement

2.8

#### Facial Disability Index

2.8.1

The primary outcome measurement is the physical function score with Facial Disability Index. The Facial Disability Index is the patient-reported evaluation questionnaire that consists of a total of 10 items, which are further divided into five items related to physical function (Physical score) and five items related to social/well-being function (Social-Wellbeing score). Based on the scores of individual items, the physical function (Physical score) is calculated out of 100 points, and the social/well-being function (Social-Wellbeing score) is also calculated out of 100 points. With a total of 200 points being the maximum score, a lower score indicates a more severe functional impairment due to facial disorders (14).

#### Sunnybrook facial grading system

2.8.2

The evaluator assesses facial movement due to FNP and derives a final score within the maximum range of 100 points based on scores for 3 Resting symmetry items, scores for 5 Symmetry of Voluntary Movement items, and scores for 5 Synkinesis items (15).

#### Numeric rating scale for stiffness

2.8.3

The discomfort from stiffness experienced in four areas—the forehead, around the eyes, cheeks, and mouth—is evaluated using a numeric rating scale of 0–10 points.

#### Synkinesis assessment questionnaire

2.8.4

The total score will be calculated by evaluating the nine typical symptoms of associated movements on a scale of 1–5 points. Divide the total score by 45 and multiply by 100 to evaluate the score out of 100 points. A higher score indicates a more severe level of associated movements as evaluated by the patient.

#### Patient global impression of change

2.8.5

This method allows research participants to evaluate the overall subjective improvement of symptoms on a 7-point scale, ranging from “much improved” to “much worse.”

#### Euro-Qol 5-dimension 5-level

2.8.6

The EuroQol-5 Dimension (EQ-5D-5L) is a widely used indirect measurement method for calculating the quality weight of a specific health state using preference scores assigned to function levels after assessing the health state from various angles. The EQ-5D-5L consists of five items, each asking about the degree of mobility, self-care, usual activities, pain/discomfort, and anxiety/depression (16). An element of the EQ-5D, a standardized tool created by the EuroQol Group for gauging general health state, is the Visual Analogue Scale (VAS) for the EQ-5D. A vertical visual analogue scale with endpoints labeled “Best imaginable health state” at 100 and “Worst imaginable health state” at 0 is used in the VAS to quantify an individual’s self-rated health. This gives a precise assessment of the patient’s perceived health status when the test is finished (17).

#### Economic cost evaluation

2.8.7

Both formal and informal healthcare costs will be surveyed. Formal healthcare costs will collect information on the type of medical institution, the number of visits (number of visits, number of admissions, total number of hospital days), and total out-of-pocket expenses, distinguishing between outpatient and inpatient treatment. Informal healthcare costs will investigate the types and expenditure amounts for over-the-counter medications, health-functional foods, medical devices, massages, and other items.

#### Adverse events

2.8.8

Adverse reactions will be collected through research participants’ symptom reporting and researchers’ observations and will be identified by the frequency of occurrence between groups. Researchers will evaluate the causal relationship between each treatment method and the adverse effects experienced using a 6-point scale (18). (1 = related, 2 = probably related, 3 = possibly related, 4 = probably not related, 5 = definitely not related, and 6 = unknown) Moreover, all adverse effects will be classified into three levels according to Spilker’s classification method (19). (Mild (1): No treatment is required, and the participant’s daily life (function) is not significantly impaired; Moderate (2): The participant’s daily life (function) is significantly impaired, and treatment may be needed, but the condition improves after treatment; Severe (3): Severe adverse reactions require extensive treatment and may leave sequelae.)

### Statistical analysis

2.9

Statistical analysis will be performed using the Full Analysis Set (FAS) analysis group, which includes participants who have received treatment at least once, and missing values will be addressed using multiple imputations. All statistical analyses will be based on two-sided tests, with a significance level set at 5%. The SAS version 9.1.3 statistical package (SAS Institute, Cary, NC, USA) will be used as the analytical tool. Descriptive statistics will be provided for each group concerning the demographic characteristics and baseline clinical data of the participants. Comparisons between groups will be conducted using the independent t-test, the Wilcoxon rank-sum test for continuous data, and the Chi-square test or Fisher’s Exact test for categorical data. For the analysis of secondary efficacy evaluation variables in Weeks 6 & 16 (secondary endpoint), the same method as the primary efficacy evaluation variables will be used. The paired t-test or Wilcoxon signed-rank test will also be employed to analyze the differences in pre- and post-treatment measurements within each group. The repeated measured Analysis of Variance (repeated measures ANOVA) will be used to assess the interaction between time and group over time.

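### The only analysis set leaves out randomised participants who never start treatment, although the arm is known before the first session

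*Protocol article*

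**What the plan says.** Section 2.9 (Statistical analysis) bases the analysis on the "Full Analysis Set (FAS) analysis group, which includes participants who have received treatment at least once". It adds that "missing values will be addressed using multiple imputations". No set of all randomised participants is named.

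Section 2.6 (Allocation concealment) says that trial personnel "will randomly assign participants by opening the sequentially numbered, opaque envelopes". On blinding it says: "As it is not feasible to blind the interventionists and participants in this study design, evaluator blinding will be implemented". Section 2.5 has treatment follow the allocation.

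Section 2.7 gives electroacupuncture to both arms and adds thread embedding (TEA) in one: "In the TEA group, after completing the acupuncture treatment, the embedding acupuncture treatment will be carried out once a week". Section 2.8.1 defines the primary outcome through the FDI: "The Facial Disability Index is the patient-reported evaluation questionnaire".

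Table 1 places randomisation, the baseline FDI and the first session in the same column, Week 1 (Visit 1).

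**The concern.** Leaving out participants who never start treatment is harmless when the decision to start cannot depend on the allocation, as in a double-blind trial. Here it can. The participant and the interventionist know the arm before the first session, and one arm adds thread embedding at 20 points while the other does not. A control participant who had hoped for threads may leave. So may a participant allocated to TEA who does not want to begin at all. Section 2.3 lets participants withdraw at any time, and lets the unblinded investigator end participation, without limiting either to the period after the first session.

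Blinding the evaluator does not help, because this selection happens before any outcome is measured. Multiple imputation as written does not help either, because it fills gaps within the analysis set and these people are outside it. What is at stake is the comparison of the groups as randomised, on a patient-reported primary outcome.

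**Working it through.** **Inputs from the article (section 2.4).** Planned difference 9.29 points, SD 17.146, two-sided alpha 0.05, power 80%, dropout 20%, 71 per group.

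**The plan's own figure.**
- Normal approximation: n = 2 × [17.146 × (1.960 + 0.842) / 9.29]² = 53.47, so 54 per group.
- Two-sample t-test: 54.45, so 55 per group.
- With 20% dropout: 54 / 0.8 = 67.5, so 68; or 55 / 0.8 = 68.75, so 69.

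The stated 71 is slightly above both, so the sample size is not in question. I use 71 only as the size of an arm.

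**Who falls outside the set.**
- A randomised participant who leaves before any session is outside it.
- A participant who has at least one session and then leaves is inside it, and the missing outcomes are imputed.
- A participant in the TEA arm who has electroacupuncture and then declines threads is inside it on the plain wording, but section 2.9 does not say so.

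**Size of the bias.** Suppose k of the 71 participants in one arm never start, none are lost this way in the other arm, and the mean outcome of starters and non-starters differs by D points. The full-arm mean is [(71 − k) × starters' mean + k × non-starters' mean] / 71. Subtracting it from the starters' mean leaves

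bias = (k / 71) × D.

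The article gives neither k nor D. With assumed values:

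| k | D (points) | Bias (points) | Share of 9.29 |
|---|---|---|---|
| 1 | 5 | 1/71 × 5 = 0.07 | 0.8% |
| 2 | 5 | 2/71 × 5 = 0.14 | 1.5% |
| 4 | 10 | 4/71 × 10 = 0.56 | 6.1% |

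**Effect on the type I error.** Take 57 evaluable per arm (71 × 0.8 = 56.8). The standard error is 17.146 × √(2/57) = 3.21. Let D be half an SD, 0.5 × 17.146 = 8.57 points.
- k = 2: bias 2/71 × 8.57 = 0.24, and the two-sided error rises from 5.0% to about 5.1%.
- k = 4: bias 4/71 × 8.57 = 0.48, and it rises to about 5.3%.

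**Effect of the fix on sample size.** None. At the planning inputs, power by the t-test is about 82% with 57 per arm and about 89% with all 71.

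**The case against.** The strongest objection is that there will be few non-starters, perhaps none. Table 1 puts randomisation and the first session at the same visit, and that visit has no window. A non-starter would have to leave between the opening of the envelope and a session at that visit. Section 2.2 also has both groups' plans explained along with the consent documents, so someone unwilling to accept either arm can decline before randomisation. Both points stand, and they keep the size small. They do not remove the problem, since the rule still lets a known allocation decide who is analysed.

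Three stronger readings are tempting and not supported.

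- A reader might infer that everyone who refuses threads is dropped from the TEA arm. Section 2.7 has electroacupuncture come first in the session, so such a person has plausibly been treated once and stays in the set. What can be said is that the definition is unclear on this case.
- A reader might infer a large bias. With 7 non-starters in one arm and D = 15, the formula gives 7/71 × 15 = 1.48 points, 16% of 9.29. That needs about 10% of one arm to leave at the first visit with no such loss in the other, together with a difference of almost 0.9 SD. Nothing in the article points there.
- A reader might infer that analysing everyone with ordinary multiple imputation removes the bias. Non-starters would have at most baseline data. Imputation under missing at random would model them on treated participants of the same arm with similar baselines, so it corrects only the part of D that baseline predicts. This objection stands in full and shapes the fix.

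It could also be said that a separate statistical analysis plan may define the sets. It may, but the article itself states the set, so the point concerns a stated choice and not an omission.

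**Conclusion.** The point holds as a modest one. The only analysis set in the article permits exclusion after randomisation that depends on a known allocation, and the planned imputation does not cover those excluded. With 1 to 4 non-starters in one arm and an outcome difference of 5 to 10 points, the bias is about 0.07 to 0.56 points, about 1% to 6% of the planned difference. Those inputs are assumptions, as is the absence of comparable loss in the other arm. The article does not show that any such exclusion will occur, nor in which direction it would act. If everyone starts, the two sets coincide and nothing changes. The case for acting is that the remedy is cheap and standard for an open-label trial.

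**What to change.** 1. Define the primary analysis set as all randomised participants, analysed in the arm assigned.
2. Ask non-starters to complete the FDI at the scheduled times where they agree. It is a questionnaire and does not require treatment.
3. Impute the remaining outcomes with the planned multiple imputation, using the Week 1 baseline FDI in the model.
4. Add a not-at-random sensitivity analysis for non-starters, for example with delta adjustment.
5. Keep the treated-at-least-once set for safety and as a sensitivity analysis, and state whether a participant in the TEA arm who received only electroacupuncture counts as treated.
6. Report the number of non-starters by arm.

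The cost is a few more imputed values and slightly more analysis work. The sample size stays at 142. Section 2.1 has enrolment ending on 31 July 2025 and data collection on 30 November 2025, so item 2 may come too late for some or all non-starters. The other items need no new data and can be fixed before the analysis.

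### The Week 8 change in FDI physical score is compared without the baseline score as a covariate, which gives up precision that the Week 1 data would supply at no cost

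*Protocol article*

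**What the plan says.** The abstract states that "The primary outcome is a change in the physical function score of the Facial Disability Index", with Week 8 as the primary endpoint. Table 1 shows the FDI collected at Week 1 (baseline) and at Weeks 6, 8 and 16.

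Section 2.9 gives one sentence on between-group tests: "Comparisons between groups will be conducted using the independent t-test, the Wilcoxon rank-sum test for continuous data". It names no covariate. It says that secondary variables follow the method used for the primary ones, but no other sentence sets out a primary method. Repeated measures ANOVA is listed only for the group-by-time interaction. The same section says that "missing values will be addressed using multiple imputations".

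Section 2.4 plans on "the mean difference of 9.29 and the standard deviation of 17.146 for the Facial Disability Index" physical score, at two-sided 5% significance and 80% power. It sets recruitment targets by centre: "102 patients (51 in the TEA group, 51 in the control group) at the one medical center", and 20 per group at the other.

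**The concern.** A change score fixes the slope on baseline at 1. With equal SDs at the two visits, the slope of the Week 8 score on the baseline score is r, which is below 1 in practice. Subtracting the whole baseline value then adds noise that a fitted slope would remove. ANCOVA fits that slope, and its only cost is one degree of freedom.

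At stake is the width of the confidence interval for the primary treatment effect, and the chance of detecting the planned difference with the patients already budgeted. The sample size is also framed as a difference in means. A single model that estimates that difference fits the plan better than a pair of tests, one of which (the rank-sum) does not estimate a mean difference and has no estimate and standard error that pool routinely over imputed data sets.

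**Working it through.** **Inputs from section 2.4.** Difference 9.29; SD 17.146; two-sided alpha 0.05; power 80%; dropout 20%; 71 per group.

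**Inputs assumed.** The correlation r between baseline and Week 8 FDI physical score is not given; the range taken is 0.3 to 0.7. The SD is taken as equal at both visits.

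**Step 1: the plan's own figure.** The plan states: "Considering a dropout rate of 20% (11), 71 participants per group will be needed".
- Normal approximation: n = 2 × (17.146 × (1.960 + 0.842) / 9.29)² = 53.5, so 54 per group; 54 / 0.8 = 67.5, so 68.
- Exact t-test: 55 per group; 55 / 0.8 = 68.75, so 69.
- Normal n divided by the rank-sum efficiency of 0.955: 54 / 0.955 / 0.8 = 70.7, so 71. The article does not say that this was used.

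The stated 71 is therefore met or slightly exceeded, and there is no sample size error here.

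**Step 2: power of the unadjusted t-test.** Evaluable per group: 71 × 0.8 = 56.8, so 56 or 57. Standardised difference: 9.29 / 17.146 = 0.542. With 57 per group the standard error is 17.146 × √(2/57) = 3.21, and the noncentrality is 9.29 / 3.21 = 2.89. Power is 81.8% (81.1% with 56).

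**Step 3: effect of adjusting for baseline.** Let σ be the SD of the score at each visit.
- Variance of change: 2σ²(1 − r).
- Residual variance in ANCOVA: σ²(1 − r²).
- Ratio: (1 + r)/2, which is below 1 for every r below 1.

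The standard error shrinks by 1 − √((1 + r)/2), that is 19%, 13% and 8% at r = 0.3, 0.5 and 0.7, whichever SD the plan means. At r = 0.5 the gain equals 2/(1 + r) = 1.33 times the patients.

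**Step 4: power with 57 per group.** Section 2.4 does not say which SD 17.146 is, so both readings are shown. ANCOVA uses 2 × 57 − 3 = 111 degrees of freedom.

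If 17.146 is the SD of change, the ANCOVA SD is 17.146 × √((1 + r)/2):

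| r | ANCOVA SD | Unadjusted change | ANCOVA |
|---|---|---|---|
| 0.3 | 13.82 | 81.8% | 94.5% |
| 0.5 | 14.85 | 81.8% | 91.2% |
| 0.7 | 15.81 | 81.8% | 87.5% |

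If 17.146 is the SD of the score, the change SD is 17.146 × √(2(1 − r)) and the ANCOVA SD is 17.146 × √(1 − r²):

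| r | Change SD | ANCOVA SD | Unadjusted change | ANCOVA |
|---|---|---|---|---|
| 0.3 | 20.29 | 16.36 | 67.9% | 85.2% |
| 0.5 | 17.15 | 14.85 | 81.8% | 91.2% |
| 0.7 | 13.28 | 12.24 | 95.9% | 98.0% |

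**Step 5: centre.** If centre explained 1%, 5% or 10% of the variance (assumed), adding it alone would move power with 56 per group from 81.1% to 81.5%, 83.0% or 85.0%.

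**Step 6: two tests named.** In a simulation under no effect (20,000 trials, 56 per group), always taking the more favourable of the two tests gave a type I error of 5.9% for normal data and about 6.6% for skewed or heavy-tailed data. Choosing by a fixed normality check gave 5.0% to 5.1%.

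**The case against.** The strongest reply is that nothing stated is wrong. A t-test on change is valid and unbiased under randomisation, and it reaches the planned power. The preference for ANCOVA is then about efficiency, and its size depends on a correlation that the article does not give. All of this stands. It limits the point to precision but does not remove it, because ANCOVA gains on both readings of the SD across the range shown. Nor is a covariate a detail left for a later document: it would replace the comparison that section 2.9 states.

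Three stronger readings are tempting, and the document does not support them.

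- *The analysis ignores baseline.* It does not: the primary outcome is a change, so baseline enters by subtraction.
- *Standard errors are too wide because centre is left out.* The targets by centre, and the random allocation table that section 2.5 attributes to the two institutes, suggest allocation by centre. Stratification is not stated outright, however, and section 2.4 allows competitive recruitment. The size of any centre effect is unknown.
- *The result can choose the p-value.* Section 2.9 pairs parametric and non-parametric tests throughout, which suggests selection by distribution. The article condenses a fuller protocol, where a selection rule may sit. Even the worst case in Step 6 adds only about 0.9 to 1.6 points to 5%.

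**Conclusion.** The point holds as an avoidable loss of precision in the primary comparison, and it is worth correcting. It is not a bias, a type I error failure or a sample size error. With 57 evaluable per group, baseline adjustment adds about 6 to 13 points of power if 17.146 is the SD of change, and about 2 to 17 points if it is the SD of the score. Under the second reading with r below 0.5, the unadjusted change analysis would itself fall below 80%, which is a further reason to adjust; the article does not settle whether that reading applies.

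The figures rest on assumed values of r, equal SDs at both visits and 20% dropout. That ANCOVA is at least as precise does not depend on the particular r, apart from the one degree of freedom spent. The gain from centre is probably small.

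**What to change.** Name one primary analysis: ANCOVA of the Week 8 FDI physical score on group, baseline FDI physical score and centre. Using the change as response gives the same treatment estimate once baseline is in the model. Include centre because allocation appears to be organised by it, and say whether randomisation was stratified by centre. Fit the model in each imputed data set, pool by Rubin's rules, and report the adjusted mean difference with its 95% confidence interval.

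Use the same model, with each outcome's own baseline, for the continuous secondary outcomes that have a Week 1 value. The Patient Global Impression of Change has none in Table 1 and needs its own method. Keep the Wilcoxon rank-sum test as a labelled sensitivity analysis.

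The change needs no new patients, visits or data, and the sample size stays at 142. It does need a dated amendment or analysis plan entry, made before database lock and before anyone sees unblinded data. Timing matters: the article is dated November 12, 2025, and section 2.1 schedules data collection to finish by November 30, 2025. The lock status is not given.
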